In the initial stage of the first three classes of BST treatment for BN, it is crucial to establish a therapeutic alliance, engage the patients, and bypass resistance to change (Nardone and Brook Barbieri, 2010). Individuals with BN are, in fact, collaborative in their intentions, but are also hindered by the fact that they rely on their strength of will. Depending on the patients’ perceptive-reactive system – the therapist may either use the *miracle fantasy* technique (i.e., What would need to happen in your life for you to be able to say, “My problem has been resolved?”) – to induce a form of positive self-deception by building a sort of prophecy that enables clients to form a strong image of a possible life without the problem – or ask the patients to think how to voluntarily worst their situation (*how worst* technique). This results in the recognition that the behaviors designed to protect them from binging are instead high-risk maintaining factors.

Further, family members are prescribed the *conspiracy of silence* (i.e., avoid talking about or acting on the problem) to interrupt attempted solutions who may be unwittingly colluding with keeping the current eating system intact (Nardone, 2003).

In the second stage of BST treatment for BN, the primary intervention is the *paradoxical diet* in which the individual is asked to think of what they would like to eat the most and carefully prepare and eat as much of those things as they want during mealtimes. The paradoxical logic underpinning the intervention is that “the only way to get rid of temptation is to yield to it” (Wilde, 1890), thus reducing the frequency of eating in favor of the pleasure of eating, and indirectly diminishing the daily amount of food the individual consumes (Nardone and Brook Barbieri, 2010). The paradoxical diet is usually accompanied by the *if you do once you do five* paradoxical prescription (i.e., From now until the next time we see each other, every time you eat something out of your three daily meals, you will have to eat it no more and no less than five times). It is aimed at transforming the guilty pleasure of eating outside of mealtimes into torture provoking extinction (Nardone et al., 1999). The concomitant usage of these two paradoxical prescriptions usually leads to a complete unblocking of the bulimic symptomatology in a few sessions.

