## Study Aim

The present study is designed to test the long-term efficacy of the BST treatment for BN and BED by assessing eating disorder symptomatology in a non-research outpatient clinic through one-year post-treatment.

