### Procedure

The study was approved by the research ethics committee of the clinic. Screening for inclusion will be conducted for consecutive patients at admission to the clinic by a clinical psychologist and psychotherapist who will be involved in the study screening and data collection stages only. Patients who will be eligible to participate will be subsequently informed about the study and invited to take part in the study. After completing the pre-treatment assessment (baseline), patients will receive 45–50 min of BST face-to-face treatment every 2 weeks for BN or BED based on their diagnosis for an anticipated total of 8 to 10 sessions. Participants will be assessed using the outcome measure (EDE-Q) at pre-treatment (T1), post-treatment (T2; approximately 16–20 weeks after the pre-treatment assessment), 6-month follow-up (T3), and 1-year follow-up (T4). During the treatment stage (T1 and T2), assessment will be conducted in a dedicated room at the clinic, whereas follow-up assessment (T3 and T4) will be conducted online.

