### Sample Size

The minimum sample size required to conduct this study was computed by using an *a priori sample size calculator* (G^∗^Power 3.1.9.2 software (Faul et al., 2007, 2009) for Fisher *f*’s tests. Participants – both BN than BED – will be measured with the EDE-Q 6.0 (Fairburn et al., 2008) at four time points: (1) at admission to the clinic, (2) at discharge, (3) at 6-month follow-up, and (4) at one year follow-up. *Clinical diagnosis* (BN *vs.* BED) was classified as between-group variable, and *time* was classified as within-subject variable. The *a priori* statistics (partial η^2^ and correlation between measures) were derived by considering previous longitudinal studies using the EDE-Q 6.0 (Fairburn et al., 2008) as measure of the range and severity of eating disorders’ features. The *a priori* partial η^2^ was set to assume a value of 0.020 (Fairburn et al., 2009) – small effect size (Cohen, 1988; Eid et al., 2017) – that provides a Cohen’s *f* equal to 0.143. Moreover, the Type I error (α) rate was set at 0.05 (two-sided) and the Power (1 – β) was set at 0.80, according to general guidelines (Cohen, 1988). In line with previous studies, the *a priori* correlation between repeated measures was set at 0.60 (Bardone-Cone and Boyd, 2007; Rose et al., 2013). Finally, sphericity was assumed. Results showed that there is an almost 81% chance of correctly rejecting the null hypothesis of no significant effect of the interaction with 28 subjects per group for a total of 56 participants.

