### Statistical Analysis

Data analyses will be performed using the R software (R Core Team, 2014), and lme4 package (Bates et al., 2015). First, preliminary analyses will be performed to test the assumptions of parametric statistics: if (strong) violations are detected, robust methods or data transformation will be applied. The EDE-Q 6.0 will be examined with the intention-to treat (ITT) analyses approach, with missing data replaced by baseline observations carried forward (BOCF) or last observation carried forward (LOCF), assuming no improvement for non-responders, as reported in previous studies (Castelnuovo et al., 2011). Dropouts will be excluded from the study.

The independent samples *t*-test will be used to examine between-group differences (BN *vs*. BED) in the EDE-Q 6.0 variables at all time-points, with attention to changes in the scores. The chi-square statistic will be used to test the association between treatment groups and socio-demographic variables (gender, age, marital status and employment status), and correlation analysis will be used to test the association between quantitative variables. Finally, multilevel growth curve model analysis will be used to estimate the average growth trajectories from baseline to one year after treatment for the EDE-Q 6.0 scores with corrected effect sizes (Hedges’ *g*) and 95% confidence interval.

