## Discussion

This paper provides a description of a proposal to evaluate the long-term efficacy of BST for the treatment of BN and BED in a real-world setting. Whilst the superiority of BST over CBT for the long-term treatment of BED has been shown in a previous study (Jackson et al., 2018), no research has yet investigated the long-term efficacy of BST for the treatment of BN. It is expected that findings will increase knowledge of the impact of BST for BED, while – for the first time – statistically testing the long-term effects of the BST protocol for BN. Due to its novelty, no hypothesis was made about the possible contribution of BST for the treatment of BN. Instead, it has been hypothesized that BST will promote sustained remission of BED symptoms.

Despite a few limitations – including the absence of a control group and the use of a single psychological measure – the research design is adapted to the clinical setting with the aim to move research into practice. Therefore, research findings will lack of generalizability, but will be useful to generate new formal hypotheses and to develop more precise research design in real-world settings.

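### The named growth analysis runs from baseline to one year without separating therapy from follow-up, and no named analysis tests whether the gain at discharge is kept

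*Protocol article*

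**What the plan says.** The Study Aim section describes a study "designed to test the long-term efficacy of the BST treatment for BN and BED" through one year after treatment. The Discussion gives the only directional hypothesis: "it has been hypothesized that BST will promote sustained remission of BED symptoms". For BN it states that no hypothesis was made.

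The Procedure section sets four EDE-Q assessments: before treatment (T1), after treatment ("T2; approximately 16–20 weeks after the pre-treatment assessment"), and follow-ups at 6 months (T3) and 1 year (T4).

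For the course over time, Statistical Analysis names one model: "multilevel growth curve model analysis will be used to estimate the average growth trajectories from baseline to one year after treatment". The Abstract says the same. Neither place says whether time is linear, quadratic, piecewise or categorical. The section also plans t-tests "in the EDE-Q 6.0 variables at all time-points, with attention to changes in the scores", but these compare BN with BED. In Sample Size, time "was classified as within-subject variable" with four occasions.

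**The concern.** Sustained remission is a claim about the period after discharge: what was gained by T2 is still there at T4. A trajectory that starts at T1 also contains the fall during therapy. If both phases share one slope or one curve, that fall helps to determine the fitted values for the follow-up year. There is no control group, so within-group change is the only evidence of efficacy, and the growth model is the only named analysis that estimates it.

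A significant downward trajectory could therefore be reported as lasting benefit while patients are partly relapsing. A difference in slope between BN and BED would likewise mix a difference in response with a difference in maintenance.

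For some BN presentations the article itself describes a rapid early change: two prescriptions used together "usually leads to a complete unblocking of the bulimic symptomatology in a few sessions". That is clinical background for the non-vomiting BN types, not a predicted EDE-Q profile. It does make an early drop followed by a different course a path that the analysis should be able to represent.

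**Working it through.** **Inputs from the article.** Four assessments; T2 at 16 to 20 weeks; EDE-Q scored 0 to 6; 28 patients per diagnosis; correlation 0.60; partial eta squared 0.020; two-sided alpha 0.05.

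**Assumptions not in the article.** Follow-up counted from the end of treatment, so visits at weeks 0, 18, 44 and 70 (18 is the midpoint of 16 to 20, plus 26 and 52); the mean profiles below; SD 1.2 (range 1.0 to 1.4); equal correlation between all pairs of visits.

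**1. The article's power figure.**
- f² = 0.020/0.980 = 0.0204, so f = 0.143 as stated.
- Noncentrality = f² × N × 4/(1 - 0.60) = 0.0204 × 56 × 4/0.40 = 11.43.
- Degrees of freedom: 3 and (56 - 2) × 3 = 162.
- Power = 0.810, which agrees with the stated figure of almost 81%.

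The figure reproduces as a 3-df diagnosis-by-visit interaction, that is, with visit as a factor. A difference between two single slopes would be a 1-df test, which is not the test that was powered.

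**2. One straight line.** Slope = Σ(t - t̄)y / Σ(t - t̄)². Here t̄ = 132/4 = 33, and Σ(t - t̄)² = 33² + 15² + 11² + 37² = 2804.
- Plateau (4, 2, 2, 2): numerator -132 - 30 + 22 + 74 = -66; slope -66/2804 = -0.02354 per week. Over the 52 weeks from T2 to T4 this is -1.22. The truth is 0.
- Half the gain lost (4, 2, 2.5, 3): numerator -132 - 30 + 27.5 + 111 = -23.5; slope -0.00838 per week; T2 to T4 = -0.44. The truth is +1.00.
- All the gain lost (4, 2, 3, 4): T2 to T4 = +0.35. The truth is +2.00.

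**3. One quadratic (least squares).**
- Plateau: fitted 3.80, 2.46, 1.63, 2.12. T3 to T4 = +0.49, a false upturn, but the net T2-to-T4 change is -0.34.
- Half the gain lost: fitted 3.77, 2.53, 2.06, 3.14. T2 to T4 = +0.60, so the relapse shows but is understated.

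**4. Dependence on time coding.** With T2 at week 16 or 20, or with visits coded 0, 1, 2, 3, the line's T2-to-T4 change under the half relapse is -0.41 to -0.50. The quadratic's false T3-to-T4 rise under the plateau is 0.40 to 0.51.

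**5. How often the line would mislead (half relapse, n = 28).** SE of the mean slope = SD × √[0.40/(28 × 2804)].

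| SD | SE | slope/SE | P(significant fall), noncentral t, 27 df |
|---|---|---|---|
| 1.0 | 0.00226 | -3.71 | 0.95 |
| 1.2 | 0.00271 | -3.09 | 0.85 |
| 1.4 | 0.00316 | -2.65 | 0.72 |

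Simulation at SD 1.2 gives 84 to 85%. In the same simulated trials, the direct T4 minus T2 contrast shows significant worsening in more than 99%.

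**6. With a knot at T2 or visit as a factor.** T4 minus T2 is recovered as 0.00 (plateau) and +1.00 (half relapse). False worsening under a plateau occurs in 2.6% of runs (nominal 2.5%). The SE of T4 minus T2 in one diagnosis is SD × √(2 × 0.40/28) = 0.203 at SD 1.2. The 95% half-width is about 1.96 × 0.203 = 0.40 points (0.33 to 0.46 for SD 1.0 to 1.4).

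**The case against.** The strongest reply is that the article commits to no particular curve. A multilevel growth model in lme4 can be piecewise or can take visit as a factor, and Sample Size treats time as four occasions with no imposed shape. The form of time is a detail that an article may leave to a fuller document. This stands. A reader might infer that one smooth line or quadratic is planned, or that the analysis is unable to show sustained benefit. Neither is supported: T2, T3 and T4 are all collected, and a permitted form of the planned model answers the question.

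A second reply is that Study Design asks about improvement from baseline through one year after treatment, which a baseline-to-one-year trajectory matches, and that sustained remission is hypothesised for BED only. This also stands in part. It is why T4 minus T1 belongs beside T4 minus T2, and why the latter is only an estimate for BN. It does not explain why the one directional hypothesis has no analysis attached.

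Third, the illustrations depend on assumed means, and a quadratic does not wholly invent or hide relapse. Correct: its false signal under a plateau is confined to T3 to T4. The line greatly understates a full relapse but does not reverse its sign. Plotting the four observed means would also expose a poor fit.

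**Conclusion.** The point holds as a mismatch between hypothesis and named analysis. The article does not separate the treatment phase from the follow-up year, and it names no test of whether the discharge gain is kept. It is not a finding that a wrong curve was chosen, because no curve is stated.

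If a single straight line were used, the error could reverse the conclusion: under the assumed half relapse, -0.44 fitted against +1.00 true, with a significant overall fall in about 85% of trials at SD 1.2 (72% to 95% for SD 1.4 to 1.0). If a single quadratic were used, the main risk is a false late upturn of about 0.5 points under a plateau. These sizes rest on the assumed means, SD and correlation structure; the direction does not depend on the time coding. The sample-size figure is unaffected.

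**What to change.** Keep the lme4 model and state the form of time. Either enter visit as a four-level factor by diagnosis, which matches the 3-df interaction behind the stated power, or use a piecewise curve in actual weeks since T1 with a knot at T2.

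Name two contrasts in each diagnosis, with 95% confidence intervals: T4 minus T1 (change at one year) and T4 minus T2 (maintenance). Make T4 minus T2 the test of maintenance for BED. Report it as an estimate for BN, where no hypothesis is stated. Do not draw the maintenance conclusion from the slope of one curve.

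State also that T4 minus T2 does not rest on T2 values carried forward. Statistical Analysis allows last observation carried forward, which sets the change to zero for anyone last seen at T2 and so flattens follow-up under any form of time. A knot alone would not settle maintenance.

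The cost is wording, plus one (knot) or two (factor) more parameters per diagnosis than a straight line. No extra data are needed.

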## Discussion

This paper provides a description of a proposal to evaluate the long-term efficacy of BST for the treatment of BN and BED in a real-world setting. Whilst the superiority of BST over CBT for the long-term treatment of BED has been shown in a previous study (Jackson et al., 2018), no research has yet investigated the long-term efficacy of BST for the treatment of BN. It is expected that findings will increase knowledge of the impact of BST for BED, while – for the first time – statistically testing the long-term effects of the BST protocol for BN. Due to its novelty, no hypothesis was made about the possible contribution of BST for the treatment of BN. Instead, it has been hypothesized that BST will promote sustained remission of BED symptoms.

Despite a few limitations – including the absence of a control group and the use of a single psychological measure – the research design is adapted to the clinical setting with the aim to move research into practice. Therefore, research findings will lack of generalizability, but will be useful to generate new formal hypotheses and to develop more precise research design in real-world settings.
